#### rhG-CSF

The rhG-CSF is performed according to the guidelines [12–14]. Patients with grade 1 myelosuppression according to the CTCAE 4.0.2 criteria are follow-up for both the intervention group and the control group. Patients with grade 2 or above myelosuppression should receive rhG-CSF treatment until the WBC count and ANC return normal. Two types of adjuvant chemotherapy regimens in breast cancer, namely ddAC-wP and TAC, can lead to a high risk of FN (incidence > 20%). According to the NCCN guidelines, prophylactic rhG-CSF treatment is recommended on day 2 or days 3 to 4 after chemotherapy. In detail, 5 mcg/kg is administrated per day until neutrophil count returns normal or nearly normal level, or long-acting rhG-CSF (PEG-rhG-CSF) is given on the second day after chemotherapy.

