### Sample size {14}

In previous studies, the incidence rate of myelosuppression was 81.0% in the control group and 61.7% in the TCM decoction group [29]. The cure rate and effective rate of the moxibustion group were 84.1% and 66.4%, while those of the control group were 35.2% and 33.3% [30]. In our preliminary study, the bone marrow suppression rate (grade 2 or above) was 52% and 81% for the MD group and the control group, respectively (δ = 15%in superiority trial). Since there are no previous data supporting the combination use of moxibustion and TCM decoction, the sample size calculation was simply based on MD/MP group versus control group, assuming that the effect of combination treatment is equivalent to or better than moxibustion or decoction alone. Considering patient enrolment at a ratio of 1:1:1 for the control, MD, and MP groups, the sample size is calculated by multiple sample rate comparisons. The sample content estimation formula is as previously described [31]. Given that *α* = 0.05 and 1-*β* = 0.08, taking a 20% drop rate into account, the required total sample size is 462 cases and 154 cases in each group.

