#### Short-term efficacy

Blood routine test: Monitoring WBC count and ANC once a week during every cycle of chemotherapy.TCM-related symptom: The investigators will evaluate the TCM-related symptoms based on the scoring method (Table 3) described in “Chinese Medicine New Drug Clinical Research Guidelines (Trial)” (China Medical Science and Technology Press, 2002) every 3 months.Adverse effects: Grading on a scale of 0 to 4 according to CTCAE 4.0.2.Quality-of-life: EORTC QLQ-C30, QLQ-BR23, and TCM Constitution.

**Table 3 Tab3:** Schedule of enrolment and assessment

	Baseline	During chemotherapy (every cycle)	Follow-up after chemotherapy (month)				
	0	1–8	6	12	18	24	36
Enrolment							
Informed consent	√						
Eligibility	√						
General assessment							
Age	√						
Sex	√						
Height	√						
Weight	√	√					
Body surface area	√						
Surgical approach	√						
Chemotherapy regimen	√						
Chemotherapy strategy	√						
Pathological stage	√						
Molecular subtype	√						
ECOG PS	√	√	√	√	√	√	√
EORTC QLQ-C30	√	√					
EORTC QLQ-BR23	√	√					
TCM constitution	√	√					
Chest CT	√			√		√	√
*Breast MRI	√			√		√	√
Serum tumour biomarkers	√	√	√	√	√	√	√
Key evaluation							
Blood routine test	√	At least once per week	√	√	√	√	√
Safety examination							
Urine routine test	√	√	√	√	√	√	√
Liver function (ALT, AST, ALP, TBIL, GGT, etc.)	√	√	√	√	√	√	√
Kidney function (CR, BUN, SCR, UA, etc.)	√	√	√	√	√	√	√
Electrocardiogram	√	√	√	√	√	√	√
Adverse events		√	√	√	√	√	√
Data evaluation							
Audit medical records		√	√	√	√	√	√
Ombudsman reviews medical records		√	√	√	√	√	√
Outcome measures		√	√	√	√	√	√

*MRI assessments were conditionally performed according to the patient’s disease status

All results are recorded in the case report form. Participants who show any adverse effects will be reported and followed up by their responsible physicians.

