#### Long-term efficacy

Three-year, 5-year, and 10-year DFS and OS.Safety evaluation: Blood pressure, heart rate, heart rhythm, respiratory rate, blood routine test, and liver and kidney functions are assessed on a scale of four levels.
Level 1: Safe—no adverse reactions; no abnormalities in safety indicators.Level 2: Comparatively safe—mild adverse reactions are observed; treatment can be continued without any intervention; no abnormality in safety indicators.Level 3: Safe issues arise—moderate adverse reactions or mild abnormalities in safety indicators are observed; treatment can be continued with suitable intervention.Level 4: Serious adverse reactions—study abortion due to serious adverse reactions; safety indicators are remarkably abnormal.

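### The four-level safety scale has gaps and an ambiguous top level that depends partly on a stopping decision, so some patients can be placed only at the discretion of unblinded physicians

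*Protocol article*

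**What the plan says.** Under Long-term efficacy, the protocol article lists vital signs and laboratory tests as safety indicators: "blood routine test, and liver and kidney functions are assessed on a scale of four levels". The levels are:

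- Level 1: "no adverse reactions; no abnormalities in safety indicators".
- Level 2: "mild adverse reactions are observed; treatment can be continued without any intervention; no abnormality in safety indicators".
- Level 3: "moderate adverse reactions or mild abnormalities in safety indicators are observed; treatment can be continued with suitable intervention".
- Level 4: "study abortion due to serious adverse reactions; safety indicators are remarkably abnormal".

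A second system runs alongside. For adverse effects, Short-term efficacy specifies "Grading on a scale of 0 to 4 according to CTCAE 4.0.2", and Outcomes {12} applies the same criteria to adverse reactions. The article does not say how the two systems map onto each other.

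Two other sections matter. Who will be blinded {17a} and Follow-up schedule both leave physicians unblinded when they assess outcomes. Criteria for discontinuing or modifying allocated interventions {11b} leaves dose reduction or discontinuation to the physician, with reference to guidelines, or to the participant's request.

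**The concern.** A scale used to compare arms should give every patient exactly one level, and the level should reflect how severe the event was. This scale does neither reliably.

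- **Missing grade.** Indicators are described as normal, mildly abnormal or markedly abnormal. Nothing is said about moderate.
- **Severity mixed with management.** Levels 2 and 3 bring in whether intervention was needed, and Level 4 brings in whether participation ended. Two patients with the same severe reaction could be placed differently because one stopped and the other did not.
- **Unclear join in Level 4.** A semicolon separates its two clauses, with neither an and nor an or.

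Where the rule gives no answer, the person completing the form must choose, and that physician knows the allocation. Moxibustion is open, and burns and skin reactions are among the adverse events listed under Secondary outcomes. A severe burn that is treated while the patient carries on could be entered at Level 3, beside mild laboratory changes. At stake is whether the safety-level table can be reproduced and compared between arms.

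**Working it through.** The article gives no figure to reproduce, so the check is to apply the definitions to every possible case.

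**Inputs.** The definitions come from Long-term efficacy. Reaction: none, mild, moderate, severe (4). Indicator abnormality: none, mild, moderate, marked (4). Treatment: continued without intervention, continued with intervention, stopped (3). Combinations: 4 × 4 × 3 = 48.

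**Readings.** Level 3 is read strictly (a moderate reaction or mild abnormality, with nothing worse present) or literally (either suffices, whatever else is present). Level 4 is read as AND (both clauses needed) or OR (either is enough). Level 1 covers 3 combinations and Level 2 covers 1 on every reading.

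**Combinations with no level**

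| Level 3 / Level 4 | Placed (Levels 1 + 2 + 3 + 4) | No level |
|---|---|---|
| Strict / AND | 3 + 1 + 4 + 1 = 9 | 48 − 9 = 39 |
| Strict / OR | 3 + 1 + 4 + 15 = 23 | 48 − 23 = 25 |
| Literal / AND | 3 + 1 + 7 + 1 = 12 | 48 − 12 = 36 |
| Literal / OR | 3 + 1 + 7 + 15 − 1 = 25 | 48 − 25 = 23 |

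The 1 subtracted in the last row is a moderate reaction with a marked abnormality, continued with intervention. It qualifies for Levels 3 and 4 at once.

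**The cases that matter, number with no level**

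| Case | Strict / AND | Strict / OR | Literal / AND | Literal / OR |
|---|---|---|---|---|
| Moderate abnormality, treatment continued (8) | 8 | 8 | 7 | 7 |
| Severe reaction, continued, indicators not marked (6) | 6 | 6 | 5 | 5 |
| Mild reaction, intervention needed, indicators normal (1) | 1 | 1 | 1 | 1 |
| Marked abnormality, treatment continued (8) | 8 | 0 | 7 | 0 |

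The first three rows are gaps on every reading, with two exceptions under the literal reading. In row one, a moderate abnormality escapes if a moderate reaction is also recorded and intervention is given. In row two, a severe reaction enters Level 3 through an accompanying mild abnormality, which ignores the severe reaction. The fourth row turns wholly on the semicolon. In Levels 1 and 2 the semicolons join conditions that must all hold, which favours AND, but the text does not settle it.

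The combinations are not equally likely and some are implausible, so these counts show where the rule fails and do not estimate the proportion of patients affected.

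**The case against.** The strongest reply is that little depends on this scale. It is not among the outcomes in Outcomes {12} and is not named in the statistical methods. Adverse effects are CTCAE-graded in parallel. Liver and kidney function, skin reactions and burns belong to a secondary outcome, and grade 3–4 leukopenia or neutropenia and febrile neutropenia to a primary one. This stands. A reader might infer that safety by arm cannot be derived, or that harm from moxibustion or the decoction would stay hidden; the article does not support that, because the same events remain reportable by arm without the scale.

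A reader might also size the gap from Sample size {14}: "the bone marrow suppression rate (grade 2 or above) was 52% and 81% for the MD group and the control group, respectively". At 154 per group that gives 154 × 0.81 = 124.7 control and 154 × 0.52 = 80.1 MD patients, and 81 − 52 = 29 percentage points between arms. These are not counts of unclassifiable patients. Under rhG-CSF, "Patients with grade 2 or above myelosuppression should receive rhG-CSF treatment until the WBC count and ANC return normal", so grade 2 suppression recorded as a moderate adverse reaction can meet Level 3, with rhG-CSF as the intervention. The article does not split grade 2 from grades 3–4 or say how many such patients continue. Nor does it say that the scale, placed under long-term follow-up, is the toxicity measure during chemotherapy.

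Nor is it established that every severe abnormality lacks a level. If Level 4 means OR, a marked abnormality is placed there whether or not participation stops.

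Last, a condensed article may leave coding detail to the full protocol or case report form. That does not answer the point: the four definitions are stated here, and the gaps lie in what they say.

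**Conclusion.** The point holds in limited form. As written, the scale is neither exhaustive nor purely severity-based. Moderate indicator abnormalities (unless also recorded as moderate reactions), severe reactions with treatment continued and indicators not markedly abnormal, and mild reactions needing intervention with normal indicators have no proper level on any reading. Level 4 is ambiguous, and part of it rests on a stopping decision made by an unblinded physician or by the participant.

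The consequence is confined to the four-level safety summary; the primary haematological outcomes, the adverse-event outcome and the CTCAE grades are untouched. The share of patients affected is unknown. The conclusion assumes that the level definitions in the article are those to be applied and that the treatment clauses in Levels 2 and 3 are conditions, not commentary. It should be corrected because the rule fails when applied as stated and the remedy is close to free.

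**What to change.** Derive each patient's safety level from the worst CTCAE grade, for reactions and indicators alike, whether or not treatment continues: grade 0 is Level 1, grade 1 is Level 2, grade 2 is Level 3, and grade 3 or more is Level 4. Report stopping because of an adverse reaction as a separate item by arm. This places every graded patient once, removes the question of how Level 4's clauses join, and reconciles the two safety systems.

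Rewording only Levels 3 and 4 would not be enough, because the Level 2 gap would remain.

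The cost is the rewording of one scale and a derivation from data already on the case report form. This assumes that indicator abnormalities are graded; where only a value was recorded, the grade would have to be derived from it. More patients will appear at the highest level, which should be explained when the table is reported. Grading itself would still be done by unblinded physicians, so the change removes discretion over the level but not over the grade. It affects reporting only and alters no rule of clinical management.

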#### Follow-up schedule

All patients will undergo an 8-week follow-up on blood routine tests, liver and kidney functions, and adverse events. The detailed schedule of enrolment and assessment is listed in Table 2. In consideration of the patient’s safety, outcome assessments are not blinded to the physicians.

### Plans to promote participant retention and complete follow-up {18b}

As mentioned above in {11c}.

### Data management {19}

A data management team consisting of administrative staffs and physicians from the Yueyang Hospital is formed to monitor the study data.

### Confidentiality {27}

The patient’s names are de-identified in the database to protect the patients’ confidentiality.

### Plans for collection, laboratory evaluation, and storage of biological specimens for genetic or molecular analysis in this trial/future use {33}

This trial involves collecting biological specimens for storage. Genetic analysis with the blood samples collected is planned in our ancillary study.

## Statistical methods

### Statistical methods for primary and secondary outcomes {20a}

Data were analysed using SPSS 18.0 (SPSS, lnc., Chicago, IL) and Stata10.0 (StataCorp, College Station, Texas). Multivariate analysis was performed by multiple linear regression, COX regression, or logistic regression, where appropriate. All analyses are based on two-sided test, with *P* values < 0.05 considered as statistically significant.

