**Methods:**

This is a randomized controlled clinical trial single-blinded for TCM decoction but not moxibustion. Patients are equally divided into the control group without decoction and moxibustion treatment (control), the decoction+moxibustion group (MD), and the placebo+moxibustion group (MP), according to the following stratification factors: age (below 40s, 40s, 50s, and 60s or above), chemotherapy regimen (anthracyclines, taxanes, anthracyclines+taxane, and others), and chemotherapy strategy (adjuvant and neoadjuvant). The TCM decoction is Wenshen Shengbai Decoction. The anticipated sample size is 462 cases (154 cases in each group). All participants are expected to treat with chemotherapy and recombinant human granulocyte colony-stimulating factor (rhG-CSF). The primary outcomes include the proportion of patients with relief of leukopenia and/or neutropenia, the myelosuppression-associated serious adverse event including grade 3–4 leukopenia and/or neutropenia, and febrile neutropenia, and the dose of rhG-CSF. The secondary outcomes include chemotherapy adherence, stratified analysis, adverse reactions, quality of life by EORTC Breast-Cancer-Specific Quality of Life Questionnaire including EORTC QLQ-C30 (V3.0) and QLQ-BR23, TCM Constitution, and 3-year disease-free survival and overall survival. Baseline information including age, surgical approach, chemotherapy regimen and strategy, pathological stage, and molecular subtype will be recorded.

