### Outcomes {12}

#### Primary outcomes

Primary outcomes are as follows:
The proportion of patients with relief of leukopenia and/or neutropenia.The number and proportion of patients with relief of myelosuppression-associated SAE, defined as grade 3–4 leukopenia and/or neutropenia and FN.The median and mean duration time of relief of leukopenia and/or neutropenia.The dosing of rhG-CSF.

The grading of adverse reactions is in accordance with the CTCAE 4.0.2 criteria. Leukopenia is defined as an abnormal decrease in white blood cells of less than LLN-3.0 × 10^9^/L. Neutropenia is defined as an abnormal decrease in netrophils of less than LLN-1.5 × 10^9^/L. The definition of FN is based on the IDSA guidelines (American Society of Infectious Diseases Guide 2010 edition), which is an absolute neutrophil count (ANC) of < 500 neutrophils/mcL or an anticipated decline to ≤ 500 in the next 48 h and progress to ≥ 38.3 °C orally or ≥ 38.0 °C for a duration over 1 h.

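### Four unranked primary outcomes are each tested at two-sided 0.05: if any one counts as success, the family-wise error is about 13–19% with the tests as written, and MD versus MP is not sized

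*Protocol article*

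**What the plan says.** **Primary outcomes.** The Primary outcomes section lists four, unranked: the proportion with relief of leukopenia and/or neutropenia; the number and proportion with relief of myelosuppression-associated serious adverse events; duration ("The median and mean duration time of relief of leukopenia and/or neutropenia"); and rhG-CSF dosing. The abstract's Methods paragraph opens its list with "The primary outcomes include the proportion of patients with relief of leukopenia and/or neutropenia, the myelosuppression-associated serious adverse event" and ends with rhG-CSF dose. Duration is absent, so the abstract has three.

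**Threshold.** Section {20a} states: "All analyses are based on two-sided test, with *P* values < 0.05 considered as statistically significant". No rule says whether one or all primary outcomes must be positive.

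**Tests.** Continuous variables are compared by one-way ANOVA, or by Kruskal-Wallis with the Nemenyi test if not normal. Unordered categorical variables are compared by chi-square or Fisher's exact test. Only Nemenyi is a pairwise procedure.

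**Sizing.** Sample size {14} plans for three arms: "Considering patient enrolment at a ratio of 1:1:1 for the control, MD, and MP groups". On the comparison used, it says "the sample size calculation was simply based on MD/MP group versus control group". Its premise is that giving both treatments does at least as well as giving either one. The rates given for this are grade 2 or above bone marrow suppression, 52% in MD and 81% in control, with a margin of 15%. No rate is given for MP.

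**Blinding.** Under {17a}, participants in MD and MP are blinded to the decoction, and outcome assessments are not blinded to the physicians.

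**The concern.** A 5% threshold keeps a trial's false-positive risk at 5% only when one test decides the trial. Here four outcomes each get the full 5%, and the reader cannot tell whether one success is enough. The abstract and the main text do not even agree on how many primary outcomes there are, so duration could be presented as primary or not once results are known. Open outcome assessment makes that freedom more damaging.

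ANOVA, chi-square and Fisher's test also say only that the three arms differ somewhere. The clinical questions concern particular arms. MD versus MP is the one contrast that isolates the decoction under patient blinding, yet the sizing does not address it. A non-significant result there could be read as showing that the decoction adds nothing, when the trial was never sized to answer that.

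**Working it through.** **1. The plan's own sample size.** Inputs from {14}: control 81%, MD 52%, margin 15 points, α = 0.05, 20% loss. Power is printed as 1−β = 0.08, read here as 0.80.

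n = (z_α + z_β)² × [p₁(1−p₁) + p₂(1−p₂)] / (difference − margin)²

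= (1.645 + 0.842)² × (0.81×0.19 + 0.52×0.48) / (0.29 − 0.15)²

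= 6.183 × 0.4035 / 0.0196 = 127.3, so 128 per arm.

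128 × 1.2 = 153.6, so 154 per arm and 3 × 154 = 462. The stated figure is reproduced exactly, with α taken one-sided. This route uses one comparison, MD versus control, on one rate. A second route comes close: 81% versus 61.7%, two-sided 0.05, power 0.92, gives 122 per arm and 122/0.8 = 153 (459 in total). That route also has a single comparison with control. Neither involves MD versus MP, and neither rate is a listed primary outcome.

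**2. Family-wise error with the tests as written.** Suppose no treatment has any effect, each outcome gets one three-group test at 0.05, and any one positive counts.

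- Independent outcomes: 1 − 0.95⁴ = 18.5% for four; 1 − 0.95³ = 14.3% for the abstract's three.
- Correlated outcomes (simulated normal outcomes, three arms, common correlation ρ, four outcomes): 15.8% at ρ = 0.5 and 13.3% at ρ = 0.7.
- If all four had to be positive, the error could not exceed 5%.

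**3. If unadjusted pairwise tests are added.** Four outcomes × three contrasts = 12 tests at 0.05, with any one counting (same simulation):

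| ρ | Three-group tests only | All pairwise, unadjusted |
|---|---|---|
| 0 | 18.5% | 40.6% |
| 0.5 | 15.8% | 34.5% |
| 0.7 | 13.3% | 29.1% |

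If pairwise tests are made only after that outcome's three-group test is significant, the any-positive error under no effect stays at the middle column, because a pairwise claim then requires a significant three-group test.

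**4. MD versus MP power.** The protocol gives no MP rate, so one must be assumed. The stand-in is 61.7%, the rate {14} quotes for a decoction group in a previous study, with no grade threshold stated. MD is 52%; evaluable per arm is 154 × 0.8 = 123; the test is two-sided 0.05 with pooled variance under the null.

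- Difference = 0.617 − 0.52 = 0.097; mean rate = 0.5685.
- SE under the null = √(0.5685 × 0.4315 × 2/123) = 0.0632.
- SE under the alternative = √[(0.617×0.383 + 0.52×0.48)/123] = 0.0629.
- Power = Φ[(0.097 − 1.96 × 0.0632)/0.0629] = Φ(−0.43) = 33.5%.

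| Assumed MP rate | Power, 123 per arm | Power, 154 per arm |
|---|---|---|
| 57% | 12% | 14% |
| 61.7% | 33.5% | 40.4% |
| 66.5% | 64% | 74% |
| 70% | 83% | 90% |

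These figures are for the grade 2 or above suppression rate. Power on the four listed outcomes cannot be computed from the document.

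**The case against.** Three stronger readings are tempting, and the document does not support them.

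- **The trial has a 29–41% false-positive risk.** That needs 12 unadjusted pairwise tests, and no section specifies them. The named tests are three-group tests. For non-normal continuous data the protocol adds Nemenyi, which already adjusts across arms; this may cover duration and rhG-CSF dose. It does not adjust across outcomes, so the inflation in step 2 remains.
- **The placebo-controlled contrast has one-third power.** This puts another study's decoction rate on an arm that receives placebo plus moxibustion. Power runs from 12% to 83% for MP rates of 57% to 70% at 123 per arm. What stands is that the contrast was not sized.
- **No contrast is identified anywhere.** The sizing paragraph does name active versus control and gives its reason. That is a sizing basis, though, and the statistical methods do not carry it into a primary comparison.

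It can also be said that hierarchy and contrasts are often left to an analysis plan, and one may exist that is not shown. That answers a complaint about missing detail. This point rests on what is stated: a blanket 0.05 rule, an unranked list, and an abstract that disagrees with it. Finally, the any-one success rule is an assumption, since the protocol is silent; requiring all four would remove the inflation.

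**Conclusion.** The point holds in limited form. The stated rule does not keep the trial-level error at 5% if one positive primary outcome is enough: it is roughly three to four times nominal on the tests as written, for correlations from 0.7 down to 0. That rests on the any-one success rule and, for the correlated figures, on normal outcomes with a common correlation. The larger figures in step 3 are conditional on a testing practice that the protocol does not prescribe.

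The sized rate is not among the declared primary outcomes, and the mismatch between abstract and main text is plain. For MD versus MP the sound conclusion is that power is unknown; the one-in-three figure is a single scenario and should not be quoted as following from the plan's own rates.

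**What to change.** Make these changes before any analysis, dated ahead of access to the data:

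1. Make the primary list identical in the abstract and the Primary outcomes section.
2. Control the 5% error across that list. Either test the outcomes in a fixed prespecified order at 0.05, stopping at the first non-significant one, or test each of four at 0.05/4 = 0.0125. Alternatively, name one listed outcome as primary and move the rest to secondary.
3. Within an outcome, compare pairs of arms at that outcome's level, and only after its three-group test is significant. With three arms this holds the error within the outcome. With the 0.0125 split the total stays at or below 4 × 0.0125 = 5% for arm-specific claims too. The fixed order protects the three-group claims; arm-specific claims pooled over outcomes are not strictly held at 5% (for example, one true-null pair in the first outcome and a null second outcome could give 1 − 0.95² = 9.75% if independent).
4. State that the trial was sized for active versus control only. Report MD versus MP as an estimate with a 95% CI, so that a non-significant result is not read as no decoction effect.

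Promoting grade 2 or above suppression to sole primary would match the sizing, but it is not on the list. It would replace all four outcomes after 218 patients had been enrolled (December 2019, Trial status) under unblinded assessment. Controlling the error across the listed outcomes avoids that.

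Cost: amended wording in the protocol and analysis plan, and a stricter threshold or fewer primary claims. At 0.0125, MD versus MP power in the 61.7% scenario falls from 33.5% to 16.7%, a further reason to report it as an estimate. No extra patients.
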